**Figure 1 figure1:**
[figure not shown]
Protocol flowchart. BID: twice daily; CrCl: creatinine clearance; DVT: deep vein thrombosis; ICU: intensive care unit; 
NCC: Neuro Critical Care; NSGY: neurosurgery; Q8h: every 8 hours; qd: daily; SCD: sequential compression device; SQ: subcutaneously.

## Results

The desired timeframe for implementing the Neurosurgery VTE prophylaxis protocol is within 6 months of QI project approval, with 1 month of “adaptation time.” Adaptation time is defined as the time between training the staff involved in the project and starting the timeline for outcomes assessment. Department project approval occurred on February 16, 2023, and the project adaptation time began on August 1, 2023.

Data collection is scheduled for completion in 2024, with analysis expected by March 2025. We anticipate a 50% reduction in VTE incidence (from 2.5% to 1.25%) following implementation of a standardized department-wide cPpx protocol. The primary outcome is the incidence of VTE. To assess whether implementation of the protocol results in a meaningful improvement compared to the standard of care, we will use a pre-post design comparing outcomes in the 12 months before and 12 months after the protocol implementation. We will evaluate differences in VTE rates using chi-square or Fisher exact test to compare the proportion of VTE events pre-implementation versus post-implementation. The justification for the chi-square test is that it is appropriate for large samples with expected counts ≥5. The Fisher exact test will be used as a backup for smaller subgroup comparisons where expected frequencies are low. In order to mitigate confounding, we will use multivariable logistic regression, using VTE occurrence as the dependent variable, with covariates including patient-level and procedural risk factors such as BMI, malignancy, surgery type (cranial vs spine), and immobility. The justification is that regression modeling will help isolate any independent effects of the protocol on VTE rates. To account for continuous secondary outcomes, we will perform stratified subgroup analyses for patients with malignancy, those undergoing cranial versus spine procedures, and those receiving LMWH versus UFH. The justification for this is that we will protect against or identify subgroups that experience differential VTE risk. A stratified analysis will determine if the protocol is equally effective across populations.

Outcomes of this QI project will be reported to the Ochsner Health Department of Neurosurgery as well as hospital administration. Results will also be shared with the scientific and health care quality improvement community. Consideration of “lessons learned” and suggestions for implementing change in order to improve patient outcomes will be made. In addition, consideration of barriers to change and recommendations for improving patient care will be discussed. This project will provide an evidence base for the implementation of the proposed protocol, and its success or failure to achieve the protocol's aims will be equally important for future hospital patient care quality improvement efforts. Considering there are limited neurosurgical society guidelines on VTE prophylaxis in perioperative patients, results from this project can be used to assess the efficacy of our specific protocol in guiding future guidelines specific for patients undergoing neurosurgery. The overarching objective of this quality improvement initiative is to advance the evidence of the effectiveness of anticoagulation prophylaxis in preventing perioperative VTE morbidity and mortality. As previously identified, the determination of whether implementation of this protocol was a success compared to the current standard-of-care success criteria will be measured against a ≥50% reduction in VTE incidence compared to baseline (from 2.5% to ≤1.25%). Secondary success measures include reduction in symptomatic PE and DVT events, and improvement in protocol adherence across clinical teams.

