While the majority of VTEs are asymptomatic, symptomatic VTEs may result in serious adverse events or death [4]. Therefore, prophylaxis of VTE plays a major role in reducing adverse events and unexpected mortality in patients undergoing neurosurgery. An ACS NSQIP data query for Ochsner Department of Neurosurgery performed on August 1, 2022, for the period of July 1, 2020, to June 30, 2021, yielded incidence rates of VTE as follows: a total of 8 events per 320 total neurosurgery cases for a rate of 2.5%, whereas the predicted rate of VTE was calculated to be 2.83% and the expected rate based on the national average rate of VTE was calculated to be 3.27%. This has resulted in an OR calculation of 0.86 (95% CI 0.52-1.42). When stratified by the type of neurosurgery, the VTE incidence rate was 0.76%, where a VTE event occurred in 1 case out of a total of 132 spine neurosurgery cases. The predicted rate for spine neurosurgery was 1.78% and the expected rate for spine neurosurgery cases was 2.24%, with an OR of 0.77 (95% CI 0.37-1.61). The rate of VTE after neurosurgery for brain tumors at Ochsner was 3.52%, based on 5 cases out of 142 total brain tumor neurosurgery cases. The predicted rate of VTE incidence for patients undergoing neurosurgery for brain tumor was 3.45% and its expected rate was 3.42%, with an OR of VTE incidence among patients after brain tumor neurosurgery of 1.01 (95% CI 0.63-1.63).

Although the incidence of VTE at Ochsner Health Department of Neurosurgery is within the expected range of nationwide data [1-3], the lack of a department- or hospital-based protocol for postoperative VTE prophylaxis results in a heterogeneity of patient care and may contribute to unexpected outcomes. Current practice dictates that individual physicians apply their chosen set of VTE prophylaxis guidelines [17]. This further contributes to a heterogeneity of patient care since most guidelines provide inconsistent recommendations (Multimedia Appendix 1). This creates a gap in patient care that could potentially be bridged through a consistent set of department VTE prevention guidelines, which would aim to diminish patient care variability and reduce the incidence of VTE below the national average rates.

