## Methods

### Overview

This project is well aligned with the Institute of Medicine’s 6 domains of quality health care and was designed according to the Institute for Healthcare Improvement steps to a good QI project [22]. It aims to avoid harm to patients while being effective in providing prophylaxis according to a risk-based approach. Specifically, the adaptive design assessing outcomes and process measures and implementing incremental change on a quarterly basis ensure the safety of this QI project. Our protocol follows the Agency for Healthcare Research 2017 guidelines to ensure patient safety while implementing this protocol [23]. This quality improvement project has been designed and reported in accordance with the SQUIRE 2.0 (Standards for Quality Improvement Reporting Excellence) guidelines. SQUIRE is the most appropriate framework for reporting system-level interventions aimed at improving health care quality, safety, and outcomes. This manuscript addresses all relevant SQUIRE elements [24]. Further, this project is patient-centered and aims to ensure equitable care for patients by consistently including all eligible individuals in the protocol without discriminating based on demographics. Finally, it is a timely and efficient protocol, reducing inconsistent application of variable guidelines and thus potentially avoiding supplies and staff waste. The assessment of the impact of this protocol on VTE incidence is at 12 and 24 months post implementation, with interim analyses every 3 months to ensure continuous quality improvement. The goal is a 50% decrease in the overall VTE incidence in patients undergoing neurosurgery from 2.5% to 1.25%, with a greater decrease in incidence of VTE among patients undergoing neurosurgical procedures for malignant pathology (cranial or spine). Targeting a reduction to 1.25% represents an achievable improvement that aligns with outcomes seen in successful QI initiatives with standardized protocols [25-27]. For example, the Mercy Hospital Springfield Neurosurgery VTE quality improvement initiative found that VTE occurrence rates in neurosurgery decreased from 3.97% at the time of protocol initiation to 0.72% in January 2020 [26]. All patients admitted to the neurosurgery service for postoperative care will be managed according to the new protocol after the implementation date. The incidence of VTE among patients admitted during the previous 12 months will serve as a control.

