### Outcomes

The primary outcome measure is the rate of VTE. Benchmark data for the primary outcome is derived from ACS NSQIP VTE rates for Ochsner Neurosurgery and the nationwide ACS NSQIP VTE rate. Benchmarks are 2.5% for Ochsner Neurosurgery and 3.27% for the national incidence rate [3]. Secondary outcome measures include the rate of PE, the rate of symptomatic DVT, and the rate of PE-associated mortality.

Process measures have an impact on the primary and secondary outcomes and will include staffing at the time of VTE diagnosis, volume of patients per resident physician, and the percentage of patients at high risk. Balancing measures include the complexity of patients based on VTE risk and history of VTE despite prophylaxis, medication reconciliations, communication with other services, and volume of patients on the neurological ICU. Procedure and patient risk factors of VTE will be included in the analysis as confounding variables. Unintended consequences such as supratherapeutic anticoagulation or bleeding events, delays in mobilization or surgery due to protocol requirements, or variation in adherence will be monitored as well. The mentioned unintended consequences will be monitored through case review and clinical incident reports, and adjustments to the protocol will be made through the Plan-Do-Study-Act cycle framework.

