
Continuous improvement is built with small incremental changes, using a systematic scientific approach to test their impact and feasibility. The Plan-Do-Study-Act cycle will be used as a model on which to structure tests of change. This includes continuous analysis of errors and successes of the protocol and subsequent protocol adaptation for the duration of the project. Dynamic data will be assessed through a run chart with data points added monthly, but with interim analysis every 3 months. Interim analyses will be discussed before changing the protocol for such quality improvement adaptations. A formal statistical analysis will be performed with a *t* test comparing NSQIP and postprotocol end-of-study VTE rates at both 12 and 24 months post implementation. Stratification based on malignancy and cranial versus spine procedures will also be assessed, as will be the confounding process and balancing measures.

Missing data will be handled through checking at each interim review. Any record missing critical outcome or key covariate information will be excluded from regression analyses. In addition, we will conduct sensitivity analyses to assess the impact of any missing data on VTE rates. Discrepancies will be resolved by consensus and reported, if indicated. Interim analyses with department reports will be performed every 3 months, but every VTE event will trigger an analysis of the variables described in this protocol. Analyses will consider barriers to change and adequacy of the protocol to guide protocol modifications and continuous implementation of improvements.

Additional guidance has been incorporated to inform future iterations of the protocol, including considerations for patients with comorbid atrial fibrillation or those already on antiplatelet therapy [34]. Implemented changes will be made based on recent evidence in the literature [35].

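### At the only yearly volume given, the adjusted logistic model has about 12 VTE events for at least five terms, too few to isolate the protocol's effect reliably

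*Protocol article*

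**What the plan says.** The analysis paragraph of the Results section describes a pre-post design, "comparing outcomes in the 12 months before and 12 months after the protocol implementation". The unadjusted comparison is chi-square, with Fisher's exact test held back for sparse subgroups. To deal with confounding, "we will use multivariable logistic regression, using VTE occurrence as the dependent variable", with covariates that include "risk factors such as BMI, malignancy, surgery type (cranial vs spine), and immobility". The stated reason is that "regression modeling will help isolate any independent effects of the protocol on VTE rates". No estimator and no fallback for sparse events is given for this regression.

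The planning figures are elsewhere. The Introduction (Overview) reports one registry year, July 2020 to June 2021: "a total of 8 events per 320 total neurosurgery cases for a rate of 2.5" per cent, including 1 event in 132 spine cases and 5 in 142 brain tumor cases. The Methods (Overview) state the aim: "The goal is a 50% decrease in the overall VTE incidence in patients undergoing neurosurgery from 2.5% to 1.25" per cent. No number of cases is given for either study window.

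Two other places bear on the size of the model. Methods (Outcomes) says "Procedure and patient risk factors of VTE will be included in the analysis as confounding variables". Methods (Selecting Change) says that stratified factors will be assessed, "as will be the confounding process and balancing measures", and that records lacking key covariates are dropped from the regressions.

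**The concern.** The information in a logistic model for a rare outcome comes from the number of events, not the number of patients. With very few events spread over several covariates, it becomes likely that every event falls in one level of some covariate. Maximum likelihood then has no finite estimate for that coefficient (separation). Even when all estimates are finite, the protocol odds ratio has a wide interval.

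This matters because the article gives the model a specific job. It is meant to separate the protocol's effect from differences in case mix, and the Limitations section offers it, with stratified analyses, as the answer to bias in a nonrandomized comparison.

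**Working it through.** **Inputs.** From the article: 8/320 at baseline, 1/132 in spine, 5/142 in brain tumor, target 1.25%, four named covariates plus the protocol term. Assumed: 320 cases in each period, because no other volume is given.

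**The article's own rates.** 8/320 = 2.50%; 1/132 = 0.76%; 5/142 = 3.52%. All three reproduce.

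**Events per term.**
- Target met: 320 × 0.025 + 320 × 0.0125 = 8 + 4 = 12 events; 12/5 = 2.4 per term.
- No effect: 8 + 8 = 16 events; 16/5 = 3.2 per term.
- Dropping incomplete records can only lower these counts.

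**Chance that a term separates (Poisson, P(no events) = exp(−expected events)).**
- Protocol term: 4 events expected after implementation, exp(−4) = 0.018, or about 2%.
- Cranial versus spine: at the article's spine rate, 1 event expected before and 0.5 after, exp(−1.5) = 0.22. The 0.76% rests on a single event, so this is only a rough guide.

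**Simulation of the five-term model.** Case mix was set close to the Introduction's. Assumed and not in the article: odds ratios of 3 for cranial surgery, 2 for malignancy, 2 for immobility and 1.3 for BMI; malignancy in 10% of spine cases; immobility in 20%; continuous BMI. The closed-form spine figure is alongside.

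| Cases before/after, true OR | Expected spine events | exp(−events) | Simulated: some term separates |
|---|---|---|---|
| 320/320, 0.5 | 1.5 | 22% | 24% |
| 320/320, 1.0 | 2 | 14% | 13% |
| 320/640, 0.5 | 2 | 14% | 15% |
| 640/640, 0.5 | 3 | 5% | 5% |
| 1,000/1,000, 0.5 | 4.7 | 1% | 1% |

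At 320 per period and a true OR of 0.5, other assumptions moved the share with a separated term. It was 10%, 16% and 36% for assumed cranial odds ratios of 2, 3 and 5 in a separate set of runs. It was 22-28% across immobility prevalences of 10-30% with continuous BMI, and 38-46% with a 10% BMI category and immobility at 10-20%. One extreme case (BMI category, immobility 5%) reached 56%. The protocol term separated in about 1-2% throughout.

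**The protocol estimate at 320 per period (4,000 replicates, true OR 0.50).**
- Maximum likelihood: average OR 0.47, log-OR bias −0.063 (Monte Carlo SE 0.011), SD of the log OR 0.69, 95% Wald coverage about 97%.
- Bias relative to the effect: 0.063/0.693 = 9%. Relative to the SD: 0.063/0.69 = 0.09, about one tenth.
- The bias was no larger when another term separated (average 0.48 with separation, 0.47 without).
- Firth-penalised fit of the same model: average OR 0.51, always finite. In the main setting of the separate set of runs, root mean squared error was 0.64 against 0.69 by maximum likelihood.
- True OR 1.0: average 1.00, no bias. With 320 before and 640 after: average 0.50.

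**What that precision means.** The crude log OR at the expected counts has SE √(1/8 + 1/312 + 1/4 + 1/316) = √0.381 = 0.62 before any adjustment. With an SD of about 0.7, a true OR of 0.5 gives a typical 95% interval of exp(−0.693 ± 1.96 × 0.7), about 0.13 to 2.0.

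**The case against.** Several points can fairly be made for the plan.

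- **The event total is inferred.** The 320 cases come from a registry query for 2020-21, not from the study windows, and the protocol covers everyone admitted to the service for postoperative care. At 640 per period separation falls to about 2-5%, and a 24-month window after implementation also helps. This stands, and the conclusion is conditional on volume. But 320 is the only departmental yearly volume in the article, and the 2.5% benchmark rests on it.
- **The estimator is not named.** A penalised fit is also a multivariable logistic regression, and an analysis plan that is not shown could specify one. This stands in part. Without qualification the phrase ordinarily means maximum likelihood, and the same paragraph gives a sparse-data fallback for the unadjusted test only.
- **Little hangs on this model.** Success is judged on the crude rate reaching 1.25% or less, and Limitations already concedes residual confounding. This limits the seriousness, although the regression is still the plan's main adjustment for confounding.

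A reader might infer that separation makes the model seriously exaggerate the protocol's benefit. The figures do not support that: separation falls almost wholly on covariates, the bias is about a tenth of the SD, it is absent at no effect, and coverage stays at or above nominal. A reader might also infer a model of a dozen terms from the Outcomes and Selecting Change wording. Those passages say that further risk factors enter the analysis and that process and balancing measures are assessed; neither puts them in this regression.

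**Conclusion.** The point holds in a limited form. If each period has about 320 cases, the adjusted model is too large for its events, and standard fitting would often leave some covariate without a finite estimate. The main weakness is imprecision: even a true halving of the odds would usually come with an interval that includes no effect. The bias away from the null is real but secondary. A model in this state cannot reliably do the isolating that the article asks of it.

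The separation frequencies rest on assumed covariate prevalences and odds ratios, and the whole conclusion rests on the 320-case volume. It is a change worth making, but not one that undermines the crude comparison on which success is judged.

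**What to change.** In the analysis paragraph of the Results section:

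- Specify Firth-penalised logistic regression with profile-penalised-likelihood confidence intervals.
- Replace the open-ended covariate list with a closed one: the protocol term plus no more than the four named pre-implementation risk factors, and preferably fewer or a single risk score.
- Say that process and balancing measures stay out of this model and are reported descriptively by period. One of them, staffing at the time of diagnosis, is defined only for patients with an event and could not serve as a covariate.
- Label the adjusted result exploratory.

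This changes wording only, uses standard software and needs no new data. The price is slight shrinkage of covariate effects and fewer adjusted factors. Penalisation secures finite estimates and removes most of the small bias, but only more events would narrow the interval.

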For all patients admitted to the Neurosurgery or NCC service and undergoing a neurological surgery, use mPpx with SCD intraoperatively and until discharge. An exception is patients in whom mPpx with SCD is contraindicated, such as patients with known DVT or lower extremity injury.For patients with intracranial hemorrhage, we will obtain stability imaging at 24-48 hours before starting cPpx.For all patients admitted to the Neurosurgery or NCC service and undergoing an elective neurological surgery, provide cPpx starting at 24 hours until discharge, unless an absolute contraindication to anticoagulation is present (per #5).Check creatinine clearance (CrCl) and choose cPpx with either enoxaparin if CrCl is >30 mL/minutes or UFH if CrCl≤30 mL/minutes. Dosing for all patients is according to weight and BMI, as obesity is an independent risk factor for hypercoagulability. Small studies have shown an advantage of weight-based dosing in achieving target anti-Xa levels with enoxaparin administration [32,33]. A clinical trial has also demonstrated a reduction in VTE rates for patients on UFH cPpx when using both BMI and weight (weight>100 kg and BMI≥40 kg/m^2^) [20]. For weight-based enoxaparin prophylaxis, the standard dose is 40 mg subcutaneously daily. For patients weighing less than 50 kg, the dose is 30 mg subcutaneously daily. Patients with a BMI more than 40 kg/m² should receive 40 mg subcutaneously twice daily, and those with a BMI more than 50 kg/m² should receive 60 mg subcutaneously twice daily. For weight-based unfractionated heparin prophylaxis, the standard dose is 5000 units subcutaneously every 8 hours. Patients with a BMI more than 40 kg/m² and a weight over 100 kg should receive 7500 units subcutaneously every 8 hours.Per AAST VTE prophylaxis in the ICU (2021) [7], an absolute contraindication to cPpx for patients hospitalized with trauma is active hemorrhage or recent spine or intracranial surgery. This is in addition to absolute contraindications to therapeutic anticoagulation, including a prior complication while on anticoagulation therapy or recurrent VTE while on an adequate dose of cPpx, or ongoing risk due to life-threatening bleeding. Risk of life-threatening bleeding includes long-bone fractures, severe pelvic fractures, plus a long-bone fracture, TBI, SCI, and medical conditions predisposing to bleeding. Patients who meet these criteria will be assessed with a stability scan before inclusion in this protocol. Relative contraindications to cPpx include epidural hematoma, risk of wound complications, and neurologic decline. Patients with relative contraindications will be included in the protocol.VTE therapy will be continued until the patient is discharged from the hospital and no longer immobilized.Training on this protocol was provided to all health care providers involved in postoperative neurosurgery patient care. A flowchart is displayed in common work areas (Figure 1). This training took place between Inservice in September and October 2023.

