## Discussion

### Expected Findings

Our review of the literature (summarized in Multimedia Appendix 1) demonstrated that all published guidelines by non-neurosurgical societies are largely inconsistent. While some suggest against the use of pharmacological prophylaxis in the majority of patients undergoing neurosurgery, others suggest stratifying patients based on risk of VTE, including those with malignancy or immobilization, and providing pharmacological prophylaxis in the high-risk group. Moreover, the choice of anticoagulant is different between published guidelines, and most do not consider weight-based dosing.

In devising our protocol, we borrowed heavily from the trauma and neurocritical care literature when choosing the timing, agents, and dosing for VTE cPpx. NASS working group on VTE prophylaxis [9] notes that the safety and utility of cPpx is controversial, and the literature does not support a specific perioperative start time point nor duration of cPpx. However, the working group acknowledges that LMWH initiated on the day of surgery may be safe for patients undergoing elective spine surgery and makes a consensus-based recommendation for it in their 2009 guidelines [9]. On the other hand, the ACCP recommends initiating cPpx in trauma neurosurgical patients within 24-72 hours of admission pending a stability scan [7]. The NCC guidelines [36] alternatively note that VTE cPpx should be initiated after 24 hours of admission for patients with aneurysmal subarachnoid hemorrhage, after 48 hours for patients with intracerebral hemorrhage, and within 24-72 hours for patients with TBI, but not before. We have elected to initiate cPpx for all admitted patients on the neurosurgery service within 24-48 hours of scheduled surgery. Patients who have a contraindication to anticoagulation or are at a high risk of intracranial bleeding will enter the protocol pending a stable head computed tomography.

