In terms of the choice of agent for VTE cPpx, Nyquist et al [36] recommend prophylaxis with UFH for patients after a nontraumatic subarachnoid hemorrhage, and either UFH or LMWH in other patients with intracerebral hemorrhage or patients with neurosurgical trauma. The AAST [7], on the other hand, notes that even though LMWH and UFH have comparable bleeding complications, LMWH results in a lower incidence of PE in trauma neurosurgical patients. Consistent with this, we selected LMWH for our protocol as the primary anticoagulant agent. However, patients with poor renal function, assessed as CrCl<30 mL/minutes, will receive UFH instead.

Another critical aspect of our protocol is the introduction of weight-based dosing. Samuel et al [20] have shown that using 7500 Units of UFH in patients on the neurocritical care service who weigh >100 kg does not lead to increased complications. Similarly, Sebaaly and Covert [33] summarize the literature on dose adjustments of LMWH to 30 mg every 8 hours for patients weighing <50 kg or having a BMI of <18 years, reporting comparable complications between higher doses and lower doses of LMWH. The AAST also recommends weight-based dosing for LMWH. Although our study design does not randomize patients, it will allow us to demonstrate the practical challenges of implementing a department-wide VTE prophylaxis protocol in reducing VTE incidence and associated morbidity and mortality.

It is further important to emphasize that VTE cPpx is often used in addition to and not instead of mPpx. Although there is evidence suggesting cPpx may be more effective in reducing the risk of VTE [15,16], all of our patients receive mPpx during their admission unless contraindicated. Consequently, our QI project is not intended to assess the significance of mPpx but rather to assess whether a standardized cPpx protocol may contribute to reducing the overall incidence of VTE and DVT in our patient population.

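### The LMWH-versus-UFH subgroup is defined by a drug choice that the protocol itself changes, and separate stratum tests cannot establish equal effectiveness

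*Protocol article*

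**What the plan says.** Results describes the main analysis as a "pre-post design comparing outcomes in the 12 months before and 12 months after the protocol implementation", using chi-square or Fisher exact tests, with Fisher kept for small subgroups. It then says "To account for continuous secondary outcomes, we will perform stratified subgroup analyses" and names the strata as malignancy, "those undergoing cranial versus spine procedures, and those receiving LMWH versus UFH". The stated inference is that "A stratified analysis will determine if the protocol is equally effective across populations".

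Three other places govern who receives which agent:

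- Methods, Selecting Change (after implementation): "choose cPpx with either enoxaparin if CrCl is >30 mL/minutes or UFH if CrCl≤30 mL/minutes".
- Discussion, Expected Findings (after implementation): LMWH is the primary agent, and "patients with poor renal function, assessed as CrCl<30 mL/minutes, will receive UFH instead".
- Introduction, Overview (before implementation): "Current practice dictates that individual physicians apply their chosen set of VTE prophylaxis guidelines". Expected Findings adds that "the choice of anticoagulant is different between published guidelines, and most do not consider weight-based dosing", and that some guidelines advise against drug prophylaxis for most neurosurgical patients.

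The Methods Overview sets a goal of a larger fall in VTE among patients with malignant pathology than overall. The stratification sentence in Selecting Change lists only malignancy and cranial versus spine, not agent.

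**The concern.** A subgroup in a pre-post comparison should be defined by something the intervention does not alter. Malignancy and surgery type meet that test. The agent received does not, because the agent rule is part of the intervention. If the protocol is followed, the post-period UFH stratum is essentially the low-CrCl patients, while the pre-period UFH stratum is whoever physicians chose to treat that way. A change in VTE rate within the stratum then mixes any protocol effect with a change in case mix. Renal function is not among the regression covariates that the article names as examples. Pre-period patients given no drug belong to neither stratum, so any gain from newly treating such patients cannot appear there.

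The second issue is inference. Judging equal effectiveness, or a greater decrease in malignancy, means comparing effects between strata. One test per stratum does not do that: a significant and a non-significant stratum may have the same effect, and two non-significant strata do not show equality. At stake is a published statement that the protocol works equally, or differently, by agent or patient group when the analysis cannot support either.

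**Working it through.** **Figures in the plan.** Baseline VTE is 8/320 = 2.5%; the target is 1.25%, and 1 − 1.25/2.5 = 50%. Introduction, Overview gives 5/142 = 3.52% for brain tumour and 1/132 = 0.76% for spine. The text gives no subgroup sample size, share of patients with low CrCl, pre-period agent mix or VTE risk by renal function.

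**Step 1: can case mix alone move the agent strata?** Assume no protocol effect and 2.5% overall in both periods. Let s be the share with low CrCl and R their relative VTE risk. Then

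- rate with higher CrCl: L = 0.025 / (1 − s + sR)
- rate with low CrCl: H = R × L

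Afterwards, under full adherence, the UFH rate is H and the LMWH rate is L. All inputs other than 2.5% are assumptions; s = 5% throughout.

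*Case A: pre-period agent unrelated to CrCl, so both pre-period strata have 2.5%.*

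| R | L | H | UFH post/pre | LMWH post/pre |
|---|---|---|---|---|
| 1 | 2.50% | 2.50% | 1.00 | 1.00 |
| 1.5 | 0.025/1.025 = 2.44% | 3.66% | 1.46 | 0.98 |
| 2 | 0.025/1.05 = 2.38% | 4.76% | 1.90 | 0.95 |

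*Case B: pre-period, all low-CrCl patients and 20% of the others already received UFH; R = 2.*

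- UFH before: (0.05 × 4.76% + 0.95 × 0.20 × 2.38%) / (0.05 + 0.19) = 2.88%
- UFH after: 4.76%, ratio 1.66
- LMWH: 2.38% in both periods, ratio 1.00

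The UFH distortion shrinks when CrCl already steered the choice, the LMWH distortion then disappears, and both vanish if low CrCl carries no extra risk.

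**Step 2: what can the baseline strata show?** Two-sided Fisher tests on the plan's own counts:

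| Comparison | p |
|---|---|
| Brain tumour 5/142 v 0/142 | 0.060 |
| Spine 1/132 v 0/132 | 1.0 |
| Brain tumour 5/142 v 0/150 | 0.026 |
| Brain tumour 5/142 v 0/284 (24 months, double the cases) | 0.004 |
| Brain tumour 5/142 v 15/142 (increase) | 0.035 |
| Spine 1/132 v 8/132 (increase) | 0.036 |

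At equal period sizes, complete elimination of VTE would not reach 0.05 in either stratum. Other sizes, the 24-month data or an increase could. Brain tumour is only a proxy for the malignancy stratum, which the Methods Overview defines as malignant cranial or spine pathology.

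**Step 3: would an interaction test settle it?** Assume 320 cases per period, risk halved (2.5% to 1.25%) in one stratum and unchanged in the other, and two-sided alpha 0.05. The difference in log odds ratios is |ln(0.0125/0.9875) − ln(0.025/0.975)| = 0.706. The variance sums 1/[n p(1 − p)] over the four cells. With a 50:50 split (160 per cell), SE = √(3 × 0.2564 + 0.5063) = 1.129, z = 0.625 and power is about 10%. If the unchanged stratum is 20% or 10% of cases, power is about 8% or 7%. The interaction is the right quantity, but its confidence interval would be very wide.

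**The case against.** The strongest reply is that this is a secondary subgroup in a quality improvement project. The primary comparison and the success criterion of at least a 50% reduction do not depend on it, and the Methods list of strata omits agent altogether. That is correct and limits the weight of the point.

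Several stronger readings are tempting, but the document does not support them:

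- *The strata will show false harm with UFH and false benefit with LMWH.* The article never names low CrCl as a VTE risk factor and gives neither its prevalence nor the earlier agent mix. Direction and size are assumptions. At 5% of 320 cases the post-period UFH stratum would be 16 patients with about 16 × 4.76% = 0.8 expected events, so chance would swamp a ratio of 1.9.
- *The post-period UFH stratum holds only low-CrCl patients.* That needs full adherence, and the Outcomes section expects adherence to vary.
- *No subgroup result could be significant.* Step 2 shows otherwise.
- *The article claims equal or greater effects.* It states a goal for malignancy and poses a question about equality. The fault is in promising that stratification will answer that question.
- *Length of stay will go unanalysed.* A method for it may sit in an analysis plan not shown. Only the stated rationale is wrong.

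The article also does not spell out that the agent strata are compared pre against post. The design and the sentence on equal effectiveness point that way. The alternative, LMWH against UFH after implementation only, would be confounded by renal function, so neither reading rescues the stratum.

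**Conclusion.** The point holds in limited form. Agent received is not a baseline characteristic here: physician choice fixed it before implementation and CrCl fixes it afterwards. The pre and post members of each agent stratum are therefore not comparable, and this conclusion needs no numerical assumption. The amount of bias is unknown. The illustrative UFH ratios of about 1.5 to 1.9 rest on 5% low CrCl, 1.5 to 2 times the risk and agent choice unrelated to CrCl. The ratio is 1.66 in the steered example at double risk, and 1.00 if low CrCl adds no risk.

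Separately, the promise that stratified analysis will establish whether effectiveness is equal is wrong as written. It would remain out of reach even with an interaction test, whose power is about 7% to 10% under the assumptions shown. Introducing subgroups as the way to handle continuous secondary outcomes is also a mistake, because stratifying does not analyse a continuous outcome. The primary analysis is unaffected.

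**What to change.** 1. Replace the agent-received stratum with renal function measured before prophylaxis, defined identically in both periods. First reconcile the cut-point: Selecting Change gives UFH at CrCl of 30 or below, Expected Findings only below 30.
2. If pre-period creatinine cannot be retrieved, drop the agent stratum. That also brings Results into line with the stratification list in Selecting Change.
3. For the retained subgroups, report the period-by-subgroup interaction with its 95% CI, label it exploratory and state that its power is very low. Treat the malignancy goal the same way.
4. Say that stratified analysis will describe results across populations, not determine whether the protocol is equally effective.
5. Remove the rationale about continuous secondary outcomes from the subgroup sentence.

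Items 3 to 5 are mainly changes of wording. Item 1 costs retrieval of pre-period laboratory values. CrCl is checked under the new protocol, but nothing in the article confirms that it is available for the earlier patients. The other cost is a more modest stated conclusion.
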